### Trial design

2.1.

The study is designed as a pilot single blinded (outcome assessors) randomized controlled trial, with 3-month follow-up, in a group of 20 subjects with dementia, in order to evaluate the improvement in patient-perceived quality of life following the use of the Paro robot integrated with traditional intervention in the older people with dementia. The Experimental Group (EG) will receive a social robotic intervention with Paro combined with traditional one. The Control Group (CG), on the other hand, will receive only the usual care. Assessment will be performed at the baseline (T0), at the end of intervention (after 12 weeks -T1) and 3 months after the end of intervention (follow-up T2).

The primary aim is to evaluate the patient-perceived improvement in terms of quality of life through Quality of Life—Alzheimer’s Disease (QoL-AD), following the use of the Paro robot, integrated with usual care carried out within the IRCCS INRCA Alzheimer’s Day Center.

The Secondary aims are the evaluation of the improvement in cognitive status of the older person with dementia, in terms of orientation, attentional-executive, visuospatial functions, detected through the Addenbrooke’s Cognitive Examination (ACE-R); the assessment of mood improvement in terms of reduction of anxiety and depression, detected through the Rating Anxiety In Dementia (RAID) scale and the Cornell Scale for Depression in Dementia (CSDD); the assessment of the older person’s acceptance of the technology through Quebec User Evaluation of Satisfaction (QUEST 2.0), semi-structured interview and analysis of physiological activation during interaction, with the Noldus Face Reader system and direct observation by the operator; the analysis of behavioral symptomatology through Neuropsychiatric Inventory (NPI); the assessment of practitioner’s acceptance of technology through Technology Acceptance Model (TAM) and the assessment of job quality through semi-structured interview.

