### Sample size

2.4.

QoL-AD (20) was used to perform a sample size calculation. Assuming an effect size of 35%, the total sample size needed to capture this effect size was estimated to be 16 subjects, assuming a statistical power of 80%, a significance level of 0.05, two groups and 3 repeated assessments (one baseline, 2 follow-ups) in a within-between interactions ANOVA model. Even assuming a drop-out rate of 20%, the total required sample size would be 20 subjects (10 in each arm).

This sample size is assumed to be more than sufficient to capture variation even for secondary outcomes for which treatment effect sizes are assumed to be similar or larger than those identified for the primary outcome.

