### Outcomes

2.7.

All outcome measures follow a standardized operating procedure. Table 1 shows the primary outcome and the secondary outcomes.

**Table 1 tab1:** Outcomes and clinical assessments.

Outcome(s)	Clinical assessment
*Primary*: Quality of life (patient)	QoL-AD
*Secondary*: Cognitive status (patient)	ACE-R
*Secondary*: Anxiety (patient)	RAID
*Secondary*: Depression (patient)	CSDD
*Secondary*: Acceptance of technology (patient)	QUEST 2.0 semi-structured interview observation by the operator
*Secondary*: Behavioral symptomatology (patient)	NPI
*Secondary*: Acceptance of technology (operator)	TAM
*Secondary*: Quality of work	Semi-structured interview

QoL-AD, Quality of Life – Alzheimer’s Disease; ACE-R, Addenbrooke Cognitive Examination; RAID, Rating Anxiety In Dementia; CSDD, Cornell Scale for Depression in Dementia; QUEST 2.0, Quebec User Evaluation of Satisfaction; NPI, Neuropsychiatric Inventory; TAM, Technology Acceptance Model.

A summary of all data collected and when these are collected is provided ion Table 2.

**Table 2 tab2:** Schedule of assessment and outcome measures.

Scale	R	T0	T1	T2
Socio-demographics checklist	X			
Mini Mental State Examination (MMSE)	X			
Addenbrooke Cognitive Examination (ACE-R)		X	X	X
Hamilton Anxiety Rating Scale (HAM-A)		X	X	X
Cornell Scale for Depression in Dementia (CSDD)		X	X	X
Quebec User Evaluation of Satisfaction (QUEST 2.0)			X	
Semi-structured interview for patient technology acceptance			X	
Quality of Life – Alzheimer’s Disease (QoL-AD)		X	X	X
Neuropsychiatric Inventory (NPI)		X	X	X
Technology Acceptance Model (TAM)			X	
Semi-structured interview for technology acceptance and workload for operator			X	

R, Recruitment; T0 = Start of intervention; T1 = End of intervention (12 weeks from T0); T2 = Follow-up at 3 months (24 weeks from T0).

The scales used during the evaluations are described below.

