### Data analysis

2.9.

A Plan of Analyses will be defined on the basis of which the analyses themselves will then be conducted. The first step of the analysis will be exploratory in nature. Descriptive analysis of the sample will be conducted using classical uni and bivariate statistical analysis techniques. Significant differences between outcomes and exposures will be compared using the Chi Square test, the Fisher Exact (in the case of categorical variables) or the *T*-test or the Anova test (in the case of comparisons of continuous variables between groups depending on whether or not they are normally distributed). In a second step, follow-up data analysis will be conducted in order to evaluate the effectiveness of the intervention. This phase of analysis will involve the use of the confounder assessment, that involves identifying and measuring potential confounding variables to ensure accurate estimation of causal effects, will be used. Techniques such as matching, stratification, or statistical adjustment through regression models will be used to account for confounding and obtain unbiased causal estimates. To assess the intervention’s effectiveness, techniques such as *t*-tests, chi-square tests, or analysis of variance (ANOVA) for continuous, categorical, or count outcomes, respectively will be used. These models compare the outcomes between the intervention and control groups, providing insights into the intervention’s impact. For the behavioral analysis, videos acquired during the interaction with Paro have been analyzed by the FaceReader software investigating facial expressions and generating a detailed report on the detected emotions, such as happiness, sadness, anger and fear. The information obtained from this analysis will be used to determine which emotion is most present during the interaction with Paro. Moreover, in the case of a semi-structured interview, data will be analyzed manually with the identification of themes, patterns, and commonalities across responses to provide insight into the research question.

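### The effectiveness test named for QoL-AD is not the model that sized the trial, gives baseline QoL-AD no specified role, and has no formally named primary visit

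*Protocol article*

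**What the plan says.** **Outcome and visits.** Section 2.1 (Trial design) states: "The primary aim is to evaluate the patient-perceived improvement in terms of quality of life through Quality of Life—Alzheimer’s Disease (QoL-AD". On timing it says: "Assessment will be performed at the baseline (T0), at the end of intervention (after 12 weeks -T1) and 3 months after the end of intervention". Table 2 in section 2.7 schedules QoL-AD at T0, T1 and T2, and its footnote defines the visits, for example "T1 = End of intervention (12 weeks from T0". No section formally calls either follow-up visit primary. The Discussion speaks of checking results at both visits and gives the later one the role of showing maintenance.

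**Sample size (section 2.4).** The required number is given as 16 evaluable subjects for an effect size of 35%, at 80% power and the 0.05 level. The model behind that number has "two groups and 3 repeated assessments (one baseline, 2 follow-ups) in a within-between interactions ANOVA model". Dropout is allowed for as follows: "Even assuming a drop-out rate of 20%, the total required sample size would be 20 subjects (10 in each arm".

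**Analysis (section 2.9).** A plan of analyses is still to be defined. For effectiveness, the section pairs t-tests with continuous outcomes, chi-square tests with categorical outcomes and ANOVA with counts, as examples rather than a closed list, and adds: "These models compare the outcomes between the intervention and control groups". A separate sentence promises regression, stratification or matching against confounding and names no variable. ANOVA is also mentioned for continuous variables in the exploratory step, but as a plain comparison between groups. No repeated-measures model, interaction, change score or baseline QoL-AD term appears.

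**The concern.** The two sections describe different tests of the same primary question. The required 16 subjects depend on a within-subject model that exploits the correlation between visits. A t-test between arms at one visit cannot use that correlation.

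QoL-AD is already measured at T0, and in many settings the baseline score is the best single predictor of the follow-up score. A trial expecting about 8 evaluable patients per arm has little precision to spare.

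A group-by-time interaction over three visits gives one test, whereas t-tests need a visit. With no visit formally named, a result at either T1 or T2 could later be presented as the primary finding.

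**Working it through.** **Inputs from section 2.4:** effect size 35%, power 80%, significance level 0.05, 2 groups, 3 assessments, 16 evaluable subjects, 20% dropout, 20 enrolled.

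**Assumptions, because the article gives none:** 35% is Cohen's f = 0.35; equal correlation rho between visits; sphericity; equal SDs; an arm difference that is zero at T0 and the same at T1 and T2.

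**1. Reproduce the plan's figure.** For the within-between interaction, lambda = f² × N × m / (1 − rho), with df1 = (2 − 1)(3 − 1) = 2 and df2 = (N − 2)(3 − 1).
- N = 16, rho = 0.5: lambda = 0.1225 × 16 × 3 / 0.5 = 11.76, df 2 and 28, power 83.7%.
- N = 14: power 77.4%. So 16 is the smallest even N that reaches 80%.
- Dropout: 16 / 0.8 = 20.

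Both stated figures reproduce, but only with the unstated rho = 0.5. Required N is 28 at rho 0, 20 at rho 0.3 and 10 at rho 0.7.

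**2. Translate f into a difference at one visit.** Arm differences of (0, d, d) have mean 2d/3 and deviations (−2/3, 1/3, 1/3)d. The interaction effects are half of these, ±(1/3, 1/6, 1/6)d in size. Their mean square is (4/36 + 1/36 + 1/36)d² / 3 = d²/18. So f = d/√18 and d = 0.35 × √18 = 1.485 SD.

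**3. Power at one named visit, 8 per arm, two-sided 0.05.**
- t-test: noncentrality 1.485 × √(8/2) = 2.970, df 14, power 78.9%.
- ANCOVA by the usual formula: divide d by √(1 − rho²), df = 2 × 8 − 3 = 13.
- The usual formula omits the cost of chance baseline imbalance, which multiplies the variance by 1 + 1/(2n − 4) = 1 + 1/12 = 1.083 on average. The stricter figure divides d by √(1.083 × (1 − rho²)). A direct simulation of ANCOVA (200,000 runs per setting) agrees with it within 0.2 points.

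| rho | t-test | sizing model, N = 16 | ANCOVA, usual formula | ANCOVA, imbalance charged |
|---|---|---|---|---|
| 0.3 | 78.9% | 69.0% | 82.0% | 79.0% |
| 0.5 | 78.9% | 83.7% | 88.6% | 86.1% |
| 0.7 | 78.9% | 97.1% | 97.0% | 95.8% |

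Example at rho 0.5: 1.485 / √(0.75 × 1.083) = 1.647; × 2 = 3.29; df 13; 86.1%.

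If all 10 per arm are evaluable and rho is 0.5, the t-test has 88.1%, the sizing model 91.9% and ANCOVA 95.1% (usual formula) or 93.9% (imbalance charged).

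**4. A different reading of 35%.** If it meant a standardised difference of 0.70 at one visit (d = 2f), 8 per arm would give 25.7% for the t-test and 32.2% for ANCOVA at rho 0.5 by the usual formula.

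**5. Two visits.** If T1 and T2 were each tested at 0.05, the chance of at least one false positive would be 1 − 0.95² = 9.75% under independence. Simulation with 8 per arm gives 9.6%, 9.1%, 8.5% and 8.0% at T1-T2 correlations of 0.3, 0.5, 0.7 and 0.8.

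**The case against.** **Baseline is not shown to be ignored.** A reader might infer that section 2.9 commits to raw, unadjusted scores. It does not say so: its list of tests is open, regression adjustment is promised, and an ANCOVA also compares outcomes between arms. A fuller plan could add the covariate. This stands. What can be said is that baseline QoL-AD has no specified role. The conflict with section 2.4 remains, because both texts are published and name different tests.

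**The t-test is valid.** A reader might infer that chance baseline differences bias it. Under randomisation they do not: it is unbiased and keeps its error rate, with chance imbalance already in its standard error. The issue is precision only.

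**The gain depends on an unknown correlation.** This stands too. At 0.3 the gain is about 3 points by the usual formula and essentially nil once imbalance is charged. At 0.7 the sizing model would have needed only 10 subjects, so the largest gains do not fit the stated N of 16 on the f = 0.35 reading.

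**No section says that T1 and T2 are each tested at 0.05.** Correct. The only test given with a significance level is one joint interaction test, which holds 5%. The inflated rate is therefore conditional. The Discussion's maintenance wording comes close to ranking the visits, but it is not a formal choice.

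**Conclusion.** The point holds in limited form. The effectiveness test that section 2.9 names for a continuous outcome is not the model in section 2.4, baseline QoL-AD is unspecified in it, and no visit is formally primary.

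On the f = 0.35 reading, with a constant difference at T1 and T2 and rho = 0.5, the t-test gives up about 5 power points against the sizing model (78.9% against 83.7%). Against ANCOVA it gives up 7 to 10 points (86.1% or 88.6%). Power therefore stays near the 80% target, and the documents do not support a claim that the mismatch by itself destroys it. Power would be far lower if 35% meant a smaller effect at one visit, but the article does not state the metric.

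The false-positive rate of about 8-9% applies only if both visits are tested separately at 0.05. The correlation, sphericity and effect pattern are all assumptions.

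**What to change.** - **Section 2.9, primary analysis:** state it as the EG minus CG difference in QoL-AD at T1 with a 95% CI, from ANCOVA at T1 or from a linear mixed model on T1 and T2 with arm, visit, arm-by-visit and baseline QoL-AD as covariate.
- **T2:** make it secondary, as evidence of maintenance, which is how the Discussion already frames it.
- **Secondary scales measured at T0** (ACE-R, CSDD, NPI and the anxiety scale): use the same baseline-adjusted form.
- **Section 2.4:** refer to this same model, and state the assumed correlation and what the 35% measures.

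The cost is wording in two sections and in the analysis plan, plus one degree of freedom for baseline. At a low correlation the covariate brings little or nothing; the single test and named visit are worth having in any case. No new data or patients are needed. The change should be made before outcome data are seen by arm.

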## Discussion

3.

The aim of the present study is to evaluate an intervention protocol for patients with dementia designed to improve primarily perceived quality of life and secondarily cognitive ability, mood, behavioral symptomatology, and the older person’s acceptance of technology. In addition, the caregiver’s acceptance of technology and workload reduction will also be assessed. We focus on patients with dementia to test whether interaction with a companion robot, specifically an animal-like robot, combined with traditional cognitive training, can actually lead to benefits in terms of improved well-being and cognitive abilities.

The intervention involves robotic training with Paro combined with traditional 12-week training for 2 sessions per week lasting 20 min each. In each session, the older person will be able to freely interact with Paro, under the supervision of the operator, who will be responsible for observing that interaction. To study the effectiveness of the intervention, we will divide the population into an experimental group (EG), which will receive the combined training, and a control group (CG), which instead, will receive only the usual care. A possible limitation of the study should be the difficulty of generalizing the study involving patients at different state of the disease, in particular with a several dementia. This aspect could be solved by involving the informal caregiver in the study.

A strength of the study is the use of the Noldus Face Reader system for the analysis of physiological activation during interaction and the use of videotaped material that will be produced after each session, thanks to which even minimal facial expressions can be captured in the subjects. In addition, the choice of a one-on-one setting is appropriate for people with behavioral and psychological symptoms of dementia to see if there is improvement in this regard (37). Another relevant aspect of the protocol is the verification of the results obtained both at the end of the intervention and 3 months after the end, to note the maintenance and generalization of the results obtained.

## Ethics and dissemination

4.

### Ethics and confidentiality

4.1.

The research underwent approval by the Ethics Committee of the Istituto Nazionale Ricovero e Cura Anziani, Istituto di Ricovero e Cura a Carattere Scientifico (IRCCS INRCA) during the meeting held on April 12, 2022. In case of any modifications to the protocol, the same Ethics Committee will be notified. This committee also acts as the data monitoring committee, periodically evaluating the progress of the protocol and ensuring compliance with the principles of the Declaration of Helsinki and Good Clinical Practice guidelines. Written informed consent will be obtained from all participants involved in the study. All personal data collected during the trial will be managed and stored in accordance with the General Data Protection Regulation (GDPR) of 2018 (38). The principal investigator will have control over the usage of the study data. All data and documentation pertaining to the trial will be stored in accordance with relevant regulatory requirements, and access to data will be restricted to authorized trial personnel.

### Dissemination of research findings

4.2.

The study findings will be used for publication in peer-reviewed scientific journals and presentations in scientific meetings. Summaries of the results will also be made available to investigators for dissemination within their clinics.

## Data availability statement

The datasets generated, used and analyzed during the trial will be available from a specific data repository or from the corresponding author upon reasonable request.

## Ethics statement

The studies involving human participants were reviewed and approved by Ethic Committee of the Istituto Nazionale Ricovero e Cura Anziani, Istituto di Ricovero e Cura a Carattere Scientifico (IRCCS INRCA). The patients/participants provided their written informed consent to participate in this study.
